## Abstract

Although computed tomography (CT) of the abdomen and pelvis (A/P) can provide crucial information for managing blunt trauma patients, liberal and indiscriminant imaging is expensive, can delay critical interventions, and unnecessarily exposes patients to ionizing radiation. Currently no definitive recommendations exist detailing which adult blunt trauma patients should receive A/P CT imaging and which patients may safely forego CT. Considerable benefit could be realized by identifying clinical criteria that reliably classify the risk of abdominal and pelvic injuries in blunt trauma patients. Patients identified as “very low risk” by such criteria would be free of significant injury, receive no benefit from imaging and therefore could be safely spared the expense and radiation exposure associated with A/P CT. The goal of this two-phase nationwide multicenter observational study is to derive and validate the use of clinical criteria to stratify the risk of injuries to the abdomen and pelvis among adult blunt trauma patients. We estimate that nation-wide implementation of a rigorously developed decision instrument could safely reduce CT imaging of adult blunt trauma patients by more than 20%, and reduce annual radiographic charges by $180 million, while simultaneously expediting trauma care and decreasing radiation exposure with its attendant risk of radiation-induced malignancy. Prior to enrollment we convened an expert panel of trauma surgeons, radiologists and emergency medicine physicians to develop a consensus definition for clinically significant abdominal and pelvic injury. In the first derivation phase of the study, we will document the presence or absence of preselected candidate criteria, as well as the presence or absence of significant abdominal or pelvic injuries in a cohort of blunt trauma victims. Using recursive partitioning, we will examine combinations of these criteria to identify an optimal “very low risk” subset that identifies injuries with a sensitivity exceeding 98%, excludes injury with a negative predictive value (NPV) greater than 98%, and retains the highest possible specificity and potential to decrease imaging. In Phase 2 of the study we will validate the performance of a decision rule based on these criteria among a new cohort of patients to ensure that the criteria retain high sensitivity, NPV and optimal specificity. Validating the sensitivity of the decision instrument with high statistical precision requires evaluations on 317 blunt trauma patients who have significant abdominal-pelvic injuries, which will in turn require evaluations on approximately 6,340 blunt trauma patients. We will estimate potential reductions in CT imaging by counting the number of abdominal-pelvic CT scans performed on “very low risk” patients. Reductions in charges and radiation exposure will be determined by respectively summing radiographic charges and lifetime decreases in radiation morbidity and mortality for all “very low risk” cases.

**Trial registration:** Clinicaltrials.gov trial registration number: NCT04937868.

## Introduction

Injuries to the abdomen and pelvis can lead to significant morbidity and mortality in patients with blunt trauma [1, 2]. Due to this potential for injury, pelvis x-rays are recommended by the American College of Surgeons Committee on Trauma’s Advanced Trauma Life Support course as an integral part of the preliminary evaluation of patients with blunt trauma [3]. In addition to pelvis x-ray and focused assessment with sonography in Trauma (FAST) scanning, abdominopelvic (A/P) CT imaging has become the most common emergency department (ED) imaging modality of the abdomen; its use has more than doubled over the past decade [4, 5].

This increase in imaging may be due to the insensitivity of physical exam findings in patients with blunt trauma, especially patients with altered mental status [6–17]. A recent large meta-analysis found that while there were a number of physical examination findings that increased the likelihood of intra-abdominal injury, no individual sign could reliably rule out injury [16]. Due to the insensitivity of physical examination, some authors have advocated liberal A/P imaging of patients with blunt trauma [8–12, 18–21]. Pelvic x-rays and FAST scanning have shown inadequate sensitivity for detecting injuries, leaving A/P CT imaging as the definitive means of assessing injury status [16]. However, there are no definite recommendations that detail which patients with blunt trauma should receive A/P CT imaging [16, 22].

It is important to note that while there has recently been a significant increase in the use of A/P CT among patients with blunt trauma, there has not been a corresponding decrease in the mortality of these patients, including those with significant abdominal-pelvic injuries (SAPI) [23, 24]. In addition, recent studies have demonstrated that selective CT imaging and serial examinations during a period of observation may negate the need for CT in many patients with blunt trauma [25–27]. The apparent lack of true clinical benefit of the increased imaging is especially striking given the risks associated with A/P CT radiation exposure; for every 725 trauma patients between 20 and 40 years of age imaged with an A/P CT, one will develop lethal cancer from the CT alone [28]. In addition to this lack of proven clinical benefit and potential patient harm, there are likely to be significant cost savings associated with more judicious application of A/P imaging [29].

It is clear that clinical decision instruments designed to guide A/P imaging are necessary, and should follow the design of similar instruments developed and validated for head, cervical spine, and chest imaging in patients with blunt trauma [30–35]. Previous investigators have proposed guidelines for abdomen-specific decision instruments, but these do not offer guidance on the use of combination A/P CTs, the form of imaging that is routinely used in trauma evaluations, and also rely on laboratory analyses–which typically provide results well after imaging decisions have been made and imaging completed [8, 9]. There is also guidance for pelvis x-rays from a large single-center study using criteria from patient history and physical examination [17]. However, this rule has yet to be prospectively validated in a multicenter study, and is not suitable for making decisions on A/P CT.

While adults make up the majority of patients with trauma, similar work has been performed in the pediatric population. In fact, the publication of a recently developed and validated multicenter decision instrument guiding the use of A/P CT in children with blunt trauma serves to highlight the feasibility and need for a similar decision instrument in adults [36]. In this multicenter study we seek to develop and validate a decision instrument to identify adults with blunt trauma who are at very low risk of significant abdominal-pelvic injuries, and for whom the use of A/P CT may be unnecessary.

## Objectives

### General design

In this prospective, cohort, multi-center study we seek to develop an imaging decision tool that will enable clinicians to identify patients with blunt trauma who are at “very low-risk” for clinically significant A/P injuries. Implementation of the decision tool will require clinicians to assess the presence or absence of specific clinical findings. Patients with a full assessment of all criteria and who exhibit none of the clinical findings will be designated as “very low-risk”. Patients who exhibit one or more of the clinical findings, as well as those for whom a complete assessment of criteria cannot be completed, will be designated as “not low-risk.” Patients who are designated as very low-risk will have negligible potential to harbor significant A/P injuries, will receive no benefit from A/P CT imaging, and will therefore be safe to exclude from A/P CT imaging. All other patients remain candidates for imaging. It is worth noting that while our project focuses on developing a rule for combined A/P CT imaging, the rule will also be suitable for evaluating patients for isolated abdominal or isolated pelvic imaging. This is a reflection of the fact that patients who are designated as low risk by our instrument will have negligible risk of either abdominal or pelvic injury, and can safely be excluded from abdominal-pelvic imaging, isolated abdominal imaging, or isolated pelvic imaging.

Classification by an optimal decision instrument will reflect a balance between the risk of imaging (malignant transformation from exposure to ionizing radiation), the costs of CT, and the risks of not imaging (potential harm from unrecognized significant injuries). Because the rate of lethal malignant transformation is low, the decision tool must exhibit high sensitivity to ensure that the missed injury rate is very low, and that virtually all patients with significant injuries are designated as “not low risk.”

To be clinically useful, the decision tool must also assign low-risk classification to as many uninjured patients as possible. This is equivalent to requiring the tool to produce as few false positive results as possible, or equivalently, exhibit high specificity. The proportion of patients who can safely be spared imaging is directly related to the instrument’s specificity, so the development process will focus on identifying a tool with the highest possible specificity.

A third aspect that must be addressed in the development process is the applicable patient cohort, which is in turn related to the intent of the rule. This is an issue that is often inadequately addressed in the development of decision instruments, but can have a profound effect on the ultimate utility of these rules. In situations where occult disease is prevalent, it may be necessary to develop a rule that applies to a broad cohort, including populations with low disease prevalence and low suspicion of disease. In addition to guiding when not to image, these instruments, sometimes referred to as two-way rules, additionally implicitly inform providers of which patients *need* to be imaged in order to reliably detect patients with occult injuries. This approach typically produces many false positive results, and can easily lead to increased imaging, which may be justified by the rule’s ability to reliably identifying occult presentations.

An alternative approach is to develop decision instruments that inform providers of which patients *do not need* imaging. This approach is favored when occult presentations are rare and providers are faced with large numbers of patients who exhibit findings that might indicate presence of injury, while the proportion of patients who actually have significant injuries is small.

In blunt trauma, the existing literature indicates that occult A/P injuries are exceptional, and that most patients with significant injuries either exhibit evidence of their injury, or exhibit characteristics that preclude a reliable assessment (e.g., intoxication or altered mentation) [23, 24]. The current status quo is that A/P CT is always or nearly always ordered for blunt trauma patients who truly have injuries, and very few abdominal/pelvic injuries remain undetected. However, along with this high detection rate of A/P injury, clinicians are also imaging a large number of patients who do not have injuries, resulting in very low yield rates of A/P CT. It is in this population that a highly sensitive decision instrument could prove of value by identifying patients who do not have injuries and who *do not need* imaging.

For this study, as with the prior NEXUS studies, we thus focus on patients who have already been identified as higher risk by the fact that the treating providers are considering ordering CT imaging. Our study cohort thus consists of patients with blunt trauma whose presentation is sufficiently concerning to merit further evaluation with A/P CT imaging, and the ultimate goal of the project is to create a decision rule that can safely decrease CT utilization among this population. We will thereby generate a *one-way rule* to be applied to patients whom clinicians were likely going to image with CT–the instrument will reliably detect all patients who have clinically significant injuries, and conversely, patients who have very low risk of injury in whom they can forego CT [37].

This approach is predicated on the assumption that occult A/P injury presentations are rare, and while the existing literature supports this idea, this assumption needs to be verified to address the potential for work-up bias. Thus, an additional component of the study is to complete an evaluation of patients with blunt trauma who do not receive A/P CT to determine how often (if ever) they are subsequently found to have significant A/P injuries that were missed on their initial assessment.

## Materials and methods

### Defining primary outcomes via expert panel review

Previous experience has shown that clinicians differ in their tolerance for missing minor injuries and in their definitions as to what constitutes a clinically significant injury. Many clinicians are comfortable using tools that occasionally miss injuries that require no intervention, provided all major injuries are identified. Other clinicians seek to identify all injuries regardless of their clinical significance [38].

To accommodate varied perspectives on clinically significant injury, we employed a modified Delphi process and convened an expert panel consisting of three trauma surgeons, three emergency medicine physicians and radiologist to define the following study outcome classifications of injuries seen on CT: clinically significant major injury, minor injury, and insignificant injury.

Our final outcome classification scheme is based in results of this Delphi process among this expert panel. Under this schema, injuries of major clinical significance consist of all abdominal and pelvic injuries requiring intervention, as well as any injury to the aorta, and any injury to the spine associated with instability or neurological compromise. Injuries that require only observation, but no intervention, will be considered clinically minor, provided they do not involve the aorta or spine, while injuries that required neither intervention nor observation will be considered insignificant. See Table 1.

**Table 1 pone.0271070.t001:** Classification of injuries based on Delphi consensus.

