**Minor injuries**
Bladder or ureteral injuries needing observation, but not requiring intervention
Bowel injuries needing observation, but not requiring intervention
Diaphragmatic injuries not requiring intervention (observation status is irrelevant)
Gynecological injuries needing observation, but not requiring intervention
Hepatobiliary injuries needing observation, but not requiring intervention
Hip fractures needing observation, but not requiring intervention
Male genital injuries needing observation, but not requiring intervention
Pancreatic injuries needing observation, but not requiring intervention
Pelvic fractures (major—excludes minor avulsion injuries and non-displaced ring fractures) not requiring intervention (observation status is irrelevant)
Pelvic fractures (minor) needing observation, but not requiring intervention
Renal injury needing observation, but not requiring intervention
Retroperitoneal injuries needing observation, but not requiring intervention
Spinal injuries (stable with no neurological compromise) needing observation, but not requiring intervention
Splenic injury needing observation, but not requiring intervention
Vascular injury (aortic) that do not need intervention or observation
Vascular injury (pelvic vessels) needing observation, but not requiring intervention
Vascular injuries (other vessels) needing observation, but not requiring intervention

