We will assign a final clinical outcome for each patient based on the results of A/P CT imaging as well as the patient’s hospital course. Patients who we designate as having injuries must have injuries evident on CT imaging. This reflects the fact that if injuries are not apparent on CT imaging, it is immaterial whether the patient underwent such imaging. Furthermore, we will classify each patient as having, in order of increasing severity: 1—no injuries (no injuries evident on CT); 2—insignificant injuries (e.g., minor bruising, small hematomas, or isolated small avulsion fractures); 3—clinically minor injuries (significant injuries that require no specific intervention); and 4—clinically major injuries (significant injuries that require specific intervention or result in patient death). Our final outcome classification will be based on the most severe type of injury sustained by each patient. We will concatenate our final outcome assignments with the criterion assessments to create our final analysis database.

We will apply chi-squared binary recursive partitioning to this data set to identify separate combinations of criteria that identify both major and minor significant abdominopelvic injuries with > 98% sensitivity and > 98% NPV, assuming such combinations exist. If more than one combination of variables exhibits the requisite sensitivity and negative predictive values for injury, the combination with the highest specificity will be adopted as the optimal low-risk decision instruments.

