### Outcome ascertainment

As mentioned previously, we will review final radiographic interpretations to determine the presence or absence of SAPI for each patient, but will classify injuries as major, minor, or insignificant based on review of procedural records. Because we are focused on assessing the need for imaging, injuries relevant for our study must be evident on A/P CT imaging. The risk classification assigned by our instrument is immaterial if an injury is not visible on CT imaging, as the injury will not be detected by such imaging.

Because there are differing opinions on the need to diagnose all injuries versus only major clinically significant injuries, we will develop two related instruments. The first will be an instrument that is highly sensitive in detecting major injuries: a goal that will improve specificity and improve the rule’s ability to decrease imaging. The tradeoff of this approach is that the rule may miss some minor injuries, and therefore be unacceptable to some clinicians.

To accommodate this perspective, we will also develop an instrument exhibiting high sensitivity in detecting all injuries, including clinically minor injuries. This instrument will likely exhibit lower specificity and a lesser ability to decrease imaging, but will enable us to provide a decision tool that will serve all clinicians regardless of their perspectives on injury detection.

Incorporating this modification enables us to provide refined definitions for our primary and secondary objectives. The primary goal of the study is to develop a decision instrument that reliably identifies patients who harbor injuries of major clinical significance that are evident on A/P CT imaging. The secondary goal of the study will be to develop a decision instrument that reliably identifies patients who harbor injuries of major or minor significance that are evident on A/P CT imaging.

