**Renal Injury**				
**Retroperitoneal Injuries**				
**Spinal Injuries–Unstable or with neurological compromise**				
**Spinal Injuries–Stable and with no neurological compromise**				
**Splenic Injuries**				
**Vascular Injuries–Aorta**				
**Vascular Injuries–Pelvic Vessels**				
**Vascular Injuries–Other Vascular Injuries**				

^a^Classification—Injury categories

No injury = No injury evident on A/P CT imaging

Clinically Insignificant injury = Unimportant injury that could be missed without significant consequences

Clinically Minor = Injury that may not require therapy, but is important to diagnose

Clinically Major = Injury that is associated with diagnostic and therapeutic implications

^b^Excludes minor avulsion injuries and non-displaced anterior ring fractures

^c^Minor fractures and non-displaced anterior pelvic ring fractures

**Interventions include:** Surgical intervention; Fracture reduction, repair or stabilization; Interventional radiology procedures or embolizations; Administration of blood or blood products; Reversal of anticoagulation; Administration of pressors

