#### Results

The respondents assigned “clinically major” importance to all injuries requiring intervention, including injuries to the bladder or ureter, bowel, diaphragm, genitals, hepatobiliary structures, hip, pancreas, pelvis, renal system, retroperitoneum, spine, spleen, and vasculature, including aorta, iliac or other vessels. Injuries to the spine that resulted in instability or neurological compromise were considered clinically major, even if they did not require intervention, as were injuries to the aorta. Respondents assigned “clinically minor” status to injuries that required observation but not intervention for the following areas: bladder or ureter, bowel, diaphragm, genitals, hepatobiliary structures, hip, pancreas, pelvis, renal system, retroperitoneum, spine (stable with no neurological compromise), spleen, and vascular injuries that do involve the aorta. Injuries that did not require intervention or observation were classified as “insignificant,” with the exception of injuries to the aorta, and injuries to the spine that involve instability or neurological compromise.

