#### Conclusions

Injuries of major clinical significance consist of all abdominal and pelvic injuries requiring intervention, as well as any injury to the aorta, and any injury to the spine associated with instability or neurological compromise. Injuries that require only observation, but no intervention, were considered clinically minor, provided they did not involve the aorta or spine, while injuries that required neither intervention nor observation were considered insignificant.

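### The major/minor boundary that defines the primary outcome is contradictory for aortic and for unstable or neurologically compromising spinal injuries managed without intervention

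*Protocol article*

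**What the plan says.** All references are to the protocol article.

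- **What is primary.** Outcome ascertainment: "The primary goal of the study is to develop a decision instrument that reliably identifies patients who harbor injuries of major clinical significance". Detecting major or minor injuries is the secondary goal.
- **Prose rule.** The expert panel section, and the Conclusions under Defining significant injuries of the abdomen and pelvis, make major every injury that needs intervention, "as well as any injury to the aorta, and any injury to the spine associated with instability or neurological compromise". Management does not matter for those two groups.
- **Table 1.** Aortic injuries, and unstable or neurologically compromising spinal injuries, are major when they need observation or intervention. The minor list includes "Vascular injury (aortic) that do not need intervention or observation". No row in any of the three lists covers an unstable or neurologically compromising spinal injury that needs neither.
- **Phase 1 grading.** Each patient is placed on a four-level scale that is merged with the criterion assessments to form the analysis database. Level 3 is "clinically minor injuries (significant injuries that require no specific intervention"; level 4 needs a specific intervention or death. There is no aortic or spinal exception.
- **Phase 2.** Outcome assessment is to be the same as in derivation.
- **Success rule.** Under Validation of the A/P CT decision instruments, the lower confidence limits for sensitivity and negative predictive value must exceed 98%.

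**The concern.** The major/minor line decides who is in the denominator of the primary sensitivity. If two statements of that line disagree, the same patient is inside the primary outcome under one and outside it under the other. When the rule catches that patient, little changes. When the rule misses that patient, the count of false negatives changes, and the success rule tolerates very few.

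Derivation is exposed too. Partitioning on major injury stops as successful once every injured patient is captured, so moving one patient across the line can change which criteria enter the rule. If the choice of definition is left until the data are in, it can be made knowing which patients were missed.

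**Working it through.** **Step 1: set the definitions side by side.** The patients in question have an aortic injury, or an unstable or neurologically compromising spinal injury, evident on CT, with no intervention and no death.

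| Injury and management | Prose (panel section, Delphi Conclusions) | Table 1 | Phase 1 scale |
|---|---|---|---|
| Aorta, neither observed nor treated | Major | Minor | Not major |
| Unstable/neurological spine, neither | Major | No row | Not major |
| Aorta, observed only | Major | Major | Minor |
| Unstable/neurological spine, observed only | Major | Major | Minor |

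In the first two rows the prose and Table 1 disagree, or Table 1 is silent. In the last two the prose and Table 1 agree, and the Phase 1 scale contradicts both.

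**Step 2: the plan's own sample-size figure.** Inputs from Sample size calculations: α = 0.05, no misses (X = N), target lower limit 0.98, stated N = 317, prevalence 5%.

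- With X = N, the printed formula P_L = N/(N + F[0.025; 2, 2N]) reduces to 0.025^(1/N).
- Setting P_L = 0.98 gives N = ln 0.025 / ln 0.98 = 182.6, so 183. The stated 317 is not reproduced. That is a separate matter and does not bear on the definitions.
- The later steps do follow: 317 / 0.05 = 6,340 per phase, and 2 × 6,340 = 12,680.

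The planned 317 is used below because it is the number the study intends to reach.

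**Step 3: how many misses 317 tolerates.** The exact (Clopper-Pearson) two-sided 95% lower limit is the 0.025 quantile of Beta(x, n − x + 1), with x major injuries caught out of n.

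| Caught / major | Lower limit | Above 98%? |
|---|---|---|
| 317/317 | 98.84% | Yes |
| 316/317 | 98.26% | Yes |
| 315/317 | 97.74% | No |

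The smallest n that passes is 277 with one miss and 359 with two, so 317 allows exactly one.

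**Step 4: move disputed, rule-negative patients across the line.**

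- No undisputed miss, one disputed patient added: 317/318, lower limit 98.26%. Still passes.
- One undisputed miss, one disputed patient added: 316/317 (98.26%, pass) becomes 316/318 (97.75%, fail).
- No undisputed miss, two disputed patients added: 317/317 (98.84%, pass) becomes 317/319 (97.75%, fail).
- In the other direction, if both misses in 315/317 (97.74%, fail) are disputed and graded minor, the result is 315/315 (98.84%, pass).

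**The case against.** The strongest reply is that a governing definition is already indicated. The panel section names the Delphi result as the final scheme and points to Table 1, so the Phase 1 wording could be shorthand for an ordered scale. On that view only one cell is in open conflict: the aortic injury needing neither observation nor intervention. This has some force, and a cross-reference would cure the Phase 1 part. But that cross-reference is not there. Read as written, the Phase 1 scale is what fills the analysis database, and it contradicts Table 1 on observed injuries. Nor can Table 1 simply be taken to govern, since the prose that cites it contradicts it on the aorta and it leaves one spinal group without a class.

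It is also fair that affected cases are traceable: the Table 2 form has separate rows for aortic and for unstable or neurologically compromising spinal injuries.

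A reader might infer more than the article supports:

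- **Death without intervention.** Table 1 does not mention it, but Phase 1 makes it major and Outcome ascertainment counts death from the injury as need for intervention. This is an omission, not a contradiction.
- **Stable spine, observed only.** The phrase "provided they did not involve the aorta or spine" seems to take all spine out of the minor class. Table 1 lists "Spinal injuries (stable with no neurological compromise) needing observation, but not requiring intervention" as minor, the Delphi Results agree, and nothing calls it major. The primary boundary is untouched.
- **Delphi Results.** The listing of "vascular injuries that do involve the aorta" as minor is evidently a dropped negative, given the sentences around it.
- **Table 2 form.** Its footnote "Clinically Major = Injury that is associated with diagnostic and therapeutic implications" is loose, but the form lists qualifying interventions, and grading is said to rest on procedural records.

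**Conclusion.** The point holds in two places: (1) aortic and unstable or neurologically compromising spinal injuries needing neither observation nor intervention, where the prose and Table 1 conflict or Table 1 is silent; and (2) the same injuries observed without intervention, where the Phase 1 scale conflicts with both. The primary outcome therefore lacks a single operative definition, and the conflict carries into validation.

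It would be tempting to say that any one re-graded patient can overturn validation. The figures do not support that. At about 317 major injuries, one disputed patient missed by the rule reverses the verdict only when exactly one other miss exists; two disputed missed patients can do so alone. The article gives no count of such patients, and how many the rule would miss is unknown, so the likely effect cannot be sized. These results assume the planned 317, exact two-sided 95% limits as in the sample-size section, and disputed patients who are rule-negative.

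**What to change.** Before outcomes are graded:

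1. Reconcile the panel section, Table 1, the Phase 1 scale and the Delphi Results and Conclusions against the tabulated Delphi votes, and issue one governing table. Neither Table 1 nor the prose should be presumed correct; the votes are not shown in the article.
2. Give that table explicit rows for aortic injury, and for unstable or neurologically compromising spinal injury, needing neither observation nor intervention.
3. State that the Phase 1 and Phase 2 outcome classes and the Table 2 form grade by that table.

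As editorial points in the same revision: restore the missing negative in the Delphi Results; limit the spinal exception in the prose to unstable or neurologically compromising injuries if, as Table 1 and the Delphi Results indicate, stable spine was voted minor; word the Table 2 footnote in terms of intervention and observation; and note in Table 1 that death from the injury counts as need for intervention.

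The cost is text, form wording and re-grading of any affected cases already classified, from records already held. No new data and no change to sample size are needed for this point.
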